**Fig. 1 Fig1:**

Formula for correction of sodium in the presence of hyperglycaemia, to be implemented when glucose > 10 mmol/L (> 180 mg/dL) [24]

#### Criteria for discontinuing or modifying allocated interventions {11b}

Overcorrection will be defined according to the European guidelines as an increment in plasma sodium of > 10 mmol/L in 24 h [7]. Overcorrection will be defined as a serious adverse event (SAE) and will prompt individualised management by the treating medical team in collaboration with the endocrinology consult service for decisions regarding re-lowering of plasma sodium with intravenous 5% dextrose therapy.

If the serum sodium rise has not exceeded 10 mmol/L in 24 h but is rising at a faster than desired rate, prophylactic intravenous 5% dextrose will be administered, per protocol. In the event that sodium concentration rises by > 6 mmol/L within 6 h of tolvaptan, or > 8 mmol/L within 12 h of tolvaptan administration, this will be initiated at a rate to match urine output, with increased frequency of sodium monitoring (Table 2) in accordance with safety advice issued by Otsuka Australia Pharmaceutical [28]. This infusion will be discontinued if the plasma sodium then falls back within the target range, and serial sodium monitoring will continue as standard protocol.

**Table 2 Tab2:** Thresholds for intervention with intravenous dextrose 5% in the context of sodium rise following tolvaptan dose

Rise in serum sodium	Time post-tolvaptan	Action
> 6 mmol/L	Within 6 h	Commence IV dextrose 5% at rate equivalent to urine output, continue to monitor frequently and cease when sodium back within target range
> 8 mmol/L	Within 12 h	
> 10 mmol/L	Within 24 h	Aim for re-lowering with bolus hypotonic fluid

In the event that daily bloods are not available for any reason, management will revert to a 1.5-L fluid restriction for both groups while awaiting further results.

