Subsequent daily study visits will evaluate the change in serum sodium over the previous 24 h, reassess volume status and then determine the dosage of tolvaptan or the limit of fluid restriction for that study day, depending on allocation. Early morning bloods will facilitate morning decision-making. Participants whose sodium level increases at the desired rate 5–8 mmol/L over 24 h will continue the same dose of their intervention. Participants whose serum sodium rise is below target will have escalation of intervention—either tolvaptan dose increase (e.g. from 7.5 to 15 mg), or reduction of fluid restriction limit (e.g. 1000 to 750 mL). Participants with decreased serum sodium despite their initial intervention will have more rapid escalation of intervention dosing (e.g. tolvaptan from 7.5 to 30 mg; or fluid restriction from 1000 to 500 ml). Participants who record a 24-h serum sodium rise > 8 mmol/L (or have required intravenous dextrose due to Na > 8 mmol above target during the 24-h period) will not receive either tolvaptan or fluid restriction the following day. Participants who achieve normalisation of serum sodium concentration (135 mmol/L or above) during the course of the trial from either arm will default to a 1500 mL ‘maintenance’ fluid restriction, unless the rise in serum Na was > 8 mmol, in which case they will have free fluid intake.

Tolvaptan doses will be administered prior to 1200 (ideally prior to 1000) to allow safe monitoring of effect during daytime hours with serum sodium measurement 6 and 12 h post dose.

Direct sodium measurement from venous blood gas samples will be preferred to determine outcomes and treatment decisions, unless this is not available. In the setting of glucose levels > 10 mmol/L (> 180 m/dl), a correction factor will be applied according to the formula published by Hillier and colleagues in 1999 (Fig. 1) [24], as endorsed by the European hyponatraemia guidelines [7]. This formula adds 2.4 mmol/l to the measured serum sodium concentration for every 5.5 mmol/L (100 mg/dl) incremental rise in serum glucose. For glucose levels below 10, this amounts to correction by 1 mmol/L or less, therefore for we have chosen to implement this correction for glucose > 10 mmol/L only for practical purposes.

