### Outcomes {12}

Primary and secondary endpoints are shown in Table 3.

**Table 3 Tab3:** Outcomes

**Primary endpoint**	• Change in serum sodium concentrations over time, from day 1 to day 4
**Secondary endpoints**	• Difference between groups of area under the curve of serial direct serum sodium measurements in mmol/L • Serum sodium increment in the first 24 and 48 h • Proportion of patients normalising serum sodium (defined as serum sodium ≥ 135 mmol/L) • Length of hospital stay • Requirement for serum sodium re-lowering with enteral or IV dextrose/water and/or desmopressin o *Main safety outcome: difference between rates of above-target correction of serum sodium leading to attenuation/reversal therapy (e.g. IV dextrose administration)* • Cognitive and functional measures at 24, 48 and 72 h (or discharge if sooner) o Confusion Assessment Method Shortform (CAM-S) score o Hyponatraemia symptom questionnaire score o Timed Up and Go test score • 30-day readmission rate • Exit questionnaire treatment satisfaction score • Serum sodium concentration 30 days after discharge

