##### Biochemistry

Sodium measurements will be performed with simultaneous indirect urea, electrolytes and creatinine and direct measurement with venous blood gas will monitor serum sodium. In patients with serum sodium below 125 mmol/L and all patients following tolvaptan administration, bloods will be performed every 6–8 h in accordance with recommendations [7, 28]. Patient with serum sodium above 125 mmol/L being managed with a fluid restriction (not tolvaptan) will have bloods every 12 h. In the event of discrepancy between these readings, the direct sodium measurement will be preferred due to increased accuracy and faster turnaround time [33]. Daily serum osmolality will be recorded. A daily urine sample at 0600 will monitor urine sodium, osmolality and specific gravity. Daily monitoring of liver function will be performed in tolvaptan recipients for safety given the small risk of liver damage identified in longer-term trials of high-dose tolvaptan used for other indications [23].

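### The main safety outcome counts a fast sodium rise only if it was treated, and the treatment and sampling rules differ by arm; overcorrection itself is recorded but is not a listed between-arm endpoint

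*Protocol article*

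**What the plan says.** **The outcome.** Under Outcomes {12}, Table 3 places the main safety outcome beneath the endpoint on needing sodium re-lowering. It is the "difference between rates of above-target correction of serum sodium leading to attenuation/reversal therapy". No line of Table 3 counts rises > 10 mmol/L in 24 h.

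**The hypothesis.** The abstract's background says that early tolvaptan should not raise the risk of overcorrection. Objectives {7} words this more broadly, as no increase in adverse events.

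**The treatment rules**, in Criteria for discontinuing or modifying allocated interventions {11b}:
- Overcorrection is > 10 mmol/L in 24 h and an SAE, whichever arm it occurs in. It "will prompt individualised management by the treating medical team in collaboration with the endocrinology consult service for decisions regarding re-lowering of plasma sodium".
- Short of that limit, a sentence that names no arm covers sodium that has not passed 10 mmol/L "but is rising at a faster than desired rate, prophylactic intravenous 5% dextrose will be administered, per protocol".
- The numeric triggers apply if sodium "rises by > 6 mmol/L within 6 h of tolvaptan, or > 8 mmol/L within 12 h of tolvaptan administration". Table 2 is titled "Thresholds for intervention with intravenous dextrose 5% in the context of sodium rise following tolvaptan dose". Its third row, an aim to re-lower after a rise > 10 mmol/L, is also timed from tolvaptan.

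**The desired rate**, in Intervention description {11a}: "Participants whose sodium level increases at the desired rate 5–8 mmol/L over 24 h will continue the same dose of their intervention". No 6-h or 12-h equivalent is given for fluid restriction.

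**The sampling**, in Biochemistry: "In patients with serum sodium below 125 mmol/L and all patients following tolvaptan administration, bloods will be performed every 6–8 h"; but "Patient with serum sodium above 125 mmol/L being managed with a fluid restriction (not tolvaptan) will have bloods every 12 h".

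The trial is open-label (Who will be blinded {17a}).

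**The concern.** An event enters the main safety outcome only after three steps: sodium rises too fast, a sample shows it, and someone treats it. Only the first is the property of the two therapies that the hypothesis is about. The second and third follow rules that depend on the arm, applied by staff who know the allocation. Two participants with the same sodium course can therefore be counted differently.

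The therapy count and the true overcorrection rate can also move in opposite directions. Dextrose started at 6 h after tolvaptan adds one event to the therapy count and may prevent a rise > 10 mmol/L.

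The Background describes guidelines as split because of overcorrection risk. The named safety comparison will be read as the answer to that question, and it answers a different one.

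**Working it through.** The plan gives no figure for this outcome, so there is none to reproduce. The check has two parts: the rules set side by side, then an illustration of size.

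**1. Rules by arm**

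| | Tolvaptan | Fluid restriction |
|---|---|---|
| Dextrose trigger at 6 h | > 6 mmol/L | none stated |
| Dextrose trigger at 12 h | > 8 mmol/L | none stated |
| General rule for fast rises | applies | applies |
| Rise > 10 mmol/L in 24 h | SAE; individualised decision, plus the Table 2 aim to re-lower | SAE; individualised decision |
| Sampling, Na < 125 mmol/L | every 6–8 h | every 6–8 h |
| Sampling, Na > 125 mmol/L | every 6–8 h after a dose | every 12 h |

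**2. One constructed sodium course.** Start at 126 mmol/L, with a rise of 7 at 6 h and of 8 at 12 h and 24 h. After tolvaptan, 7 > 6 at 6 h directs dextrose, so the participant counts. On fluid restriction above 125 mmol/L no 6-h sample is scheduled, and a rise of 8 over 24 h lies within the desired 5–8, so the participant need not count. This shows that the rules can separate identical courses. It says nothing about how often that happens.

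**3. Illustration of size**

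Inputs:
- n = 83 per arm (planned) or 34 per arm (minimum), from Table 5 of Sample size {14}.
- q = true rate of fast rises, set equal in both arms. This is an assumption; the document gives no rate for fluid restriction.
- All fast rises after tolvaptan are treated, and a share t of those on fluid restriction. This is also an assumption.

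Expected excess of counted events in the tolvaptan arm = n × q × (1 − t). For n = 83, q = 5%, t = 0.5: 83 × 0.05 × 0.5 = 2.1 participants.

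Chance of a false signal = P(two-sided Fisher p < 0.05 with tolvaptan higher), taking tolvaptan counts as Bin(n, q) and fluid-restriction counts as Bin(n, q·t). At 83 per arm:

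| q | t = 0 | t = 0.5 | t = 0.75 | t = 1 |
|---|---|---|---|---|
| 2% | 0.7% | 0.3% | 0.2% | 0.1% |
| 5% | 23.5% | 4.6% | 2.0% | 0.9% |
| 10% | 84.9% | 15.1% | 5.0% | 1.5% |

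At 34 per arm and t = 0.5: 0.3% at q = 5% and 2.7% at q = 10%.

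**4. Precision of the proposed outcome.** With no events in either arm, the Newcombe 95% interval for the difference is ±z²/(n + z²), with z² = 3.84. For n = 83: 3.84/86.84 = ±4.4 percentage points. For n = 34: 3.84/37.84 = ±10.2 points.

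**The case against.** The strongest reply is that little is lost. Overcorrection is defined without reference to arm or therapy, is an SAE, and goes to the DSMB. Daily sodium increments and any dextrose are recorded, and the 24-h and 48-h increments are listed secondary endpoints. This stands as far as data capture goes. A reader might infer from Table 3 that overcorrection on fluid restriction goes unrecorded; the document does not support that. What remains is that no listed endpoint compares the > 10 mmol/L rate between arms. The listed increments cover the first 24 and 48 h, not any 24-h window to day 4.

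Second, the arm-neutral sentence directs dextrose for fast rises on fluid restriction too, and the full protocol, not shown, may give numbers for it. This also stands. A reader might take Table 2 to mean that fast rises on fluid restriction go untreated and that a large false signal is likely. That is the t = 0 column, which the arm-neutral sentence contradicts.

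Third, q on fluid restriction may be low. Participants already correcting fast are excluded, a 24–48 h run-in removes autocorrection, and the Background calls fluid restriction ineffective in about half of cases. The overcorrection rates quoted there (such as 12.1% in a registry) are for tolvaptan and cannot stand in for q.

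Fourth, needing dextrose is a real burden of the tolvaptan strategy, and the section on retention and follow-up {18b} accepts a comparison that includes the safeguards. Agreed: that is a reason to keep the outcome, not to let it stand for overcorrection. The bias probably runs against tolvaptan, so false reassurance is not the main worry.

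Finally, the sampling gap is limited to fluid-restriction participants above 125 mmol/L, whose 12-h and morning values can still show a rise > 10 mmol/L in 24 h.

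**Conclusion.** The point holds as a mismatch between hypothesis and named outcome, with an arm-dependent element in how events are detected and treated. That part rests on the text alone and needs no assumed rate.

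The bias is likely to run against tolvaptan. Its size cannot be set from the document and is probably small. It is negligible if fast rises on fluid restriction are rare: at most 0.7% chance of a false signal at q = 2% and 83 per arm. At q = 5% the chance is about 5% with half of fluid-restriction rises treated and 2% with three quarters treated. Reaching 23.5% requires that none be treated. All of these rest on the assumed q and t, on equal true rates, and on every fast rise after tolvaptan being treated.

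The case for acting is that the trial's central safety question should have its own listed comparison, which can be had from data already collected.

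**What to change.** 1. Add to Table 3 the proportion with a sodium rise > 10 mmol/L in any 24 h up to day 4, by assigned arm and regardless of therapy, as the between-arm measure of the overcorrection hypothesis. Report the difference with its 95% interval and say that it compares strategies including rescue dextrose.
2. Add a sensitivity analysis limited to time points sampled in both arms, at least the 0600 values.
3. Keep attenuation or reversal therapy as a separate outcome, ideally split into Table 2-triggered and discretionary use. Read the two together, because tolvaptan-only dextrose can raise the therapy count while lowering the > 10 mmol/L rate.

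The cost is one line in Table 3 and a sentence in the statistical methods, with no extra blood tests. The downside is one more safety outcome, and an imprecise one: even with no events in either arm the interval is ±4.4 points at 83 per arm and ±10.2 at 34. A non-significant difference should therefore not be read as proof of safety.

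### Overcorrection has no dose clock but every Table 2 trigger does, so a 24-h rise spanning two tolvaptan doses can exceed 10 mmol/L without meeting a trigger; the dextrose stop range is also undefined

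*Protocol article*

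**What the plan says.** All references are to the protocol article.

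- **Definition (section 11b).** "Overcorrection will be defined according to the European guidelines as an increment in plasma sodium of > 10 mmol/L in 24 h". It is an SAE and "will prompt individualised management by the treating medical team in collaboration with the endocrinology consult service for decisions regarding re-lowering of plasma sodium". Neither statement mentions dose time.
- **Before that level (section 11b).** If sodium has not risen that far but "is rising at a faster than desired rate, prophylactic intravenous 5% dextrose will be administered, per protocol". The only numbers attached to this are that sodium "rises by > 6 mmol/L within 6 h of tolvaptan, or > 8 mmol/L within 12 h of tolvaptan administration".
- **Table 2.** Its caption is "Thresholds for intervention with intravenous dextrose 5% in the context of sodium rise following tolvaptan dose". All three rows (above 6 within 6 h, above 8 within 12 h, above 10 within 24 h) count hours after tolvaptan.
- **Stop rule (section 11b).** "This infusion will be discontinued if the plasma sodium then falls back within the target range". Table 2 repeats the idea. Neither place says what the range is.
- **Repeat dosing (section 11a, Table 1).** "Participants whose sodium level increases at the desired rate 5–8 mmol/L over 24 h will continue the same dose of their intervention". A participant whose sodium is still 134 mmol/L or lower loses the day's dose on account of the rise only if the preceding 24-h increment was above 8.
- **Monitoring.** Section 11a plans sodium at 6 and 12 h after each dose. The Biochemistry section plans bloods every 6–8 h after tolvaptan. The Treatment questionnaire section records a daily 24-h increment.

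**The concern.** The SAE is defined on one clock and the triggers meant to forestall it run on another. Each new dose starts a fresh count, so a rise late in the first dosing day and a rise early in the second are never added together in Table 2. The daily increment that steers titration compares one morning with the next, so it can miss the same rise.

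Three things depend on this. The main safety outcome (Table 3) is the difference in rates of above-target correction that leads to attenuation or reversal therapy, so whether such therapy is started decides the count. Under section 11a, a need for dextrose can also withhold the next day's treatment. And the DSMB can review only those SAEs that someone has recognised.

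The undefined stop range is a lesser matter. On one reading, staff would find the start and stop conditions satisfied by the same sodium value.

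**Working it through.** The plan gives no figure to reproduce; this is a check of threshold logic.

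**Inputs.** SAE: rise above 10 in 24 h (11b). Triggers: above 6 by 6 h, above 8 by 12 h and above 10 by 24 h after a dose (Table 2). Next dose allowed: preceding increment of 8 or less and sodium of 134 or less (Table 1). Dosing ideally before 1000, so 1000 is used, with samples at 1600 and 2200 (11a).

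**Part 1: rises spanning two doses.** Path A is a plain example, with the values not needed for the argument filled in. Paths B and C are more extreme (all in mmol/L).

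| Time | A | B | C |
|---|---|---|---|
| Day 1 0600 | 120 | 120 | 118 |
| Day 1 1000, dose 1 | 120 | 120 | 118 |
| Day 1 1600 | 122 | 120 | 118 |
| Day 1 2200 | 122 | 120 | 118 |
| Day 2 0600 | 127 | 128 | 126 |
| Day 2 1000, dose 2 | 127 | 128 | 126 |
| Day 2 1600 | 133 | 133 | 126 |
| Day 2 2200 | 133 | 135 | 134 |
| Day 3 0600 | 133 | 136 | 134 |

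- Increment day 1 to day 2 at 0600: A 127 − 120 = 7; B 128 − 120 = 8; C 126 − 118 = 8. Dose 2 is allowed in each.
- Clock of dose 1: the rise by 24 h is 7, 8 and 8, and by 12 h it is 2, 0 and 0. No row is met.
- Clock of dose 2 at 6 h: A 133 − 127 = 6; B 133 − 128 = 5; C 126 − 126 = 0. None is above 6.
- Clock of dose 2 at 12 h: A 6; B 135 − 128 = 7; C 134 − 126 = 8. None is above 8.
- Increment day 2 to day 3 at 0600: A 133 − 127 = 6; B 136 − 128 = 8; C 134 − 126 = 8. None is above 8.
- Largest rise within 24 h: A, 1600 to 1600, 133 − 122 = **11**; B, 2200 to 2200, 135 − 120 = **15**; C, 2200 to 2200, 134 − 118 = **16**. All exceed 10.

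Path C is the worst case found by enumerating non-decreasing whole-mmol/L paths from 118 at these sampling times, with the baseline for each dose taken at the dose or at that morning's 0600 sample. The figure is 8 (the most Table 1 tolerates before dose 2) plus 8 (the most Table 2 tolerates by 12 h after it).

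**Part 2: start against stop.** Suppose the target range is a rise of 5–8 mmol/L.

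- At 6 h: the start condition is a rise above 6. The overlap with 5–8 is above 6 up to 8. Rises of 6.5, 7 and 8 meet both conditions; 8.5, 9 and 10 meet only the start.
- At 12 h: the start condition is a rise above 8. The overlap with 5–8 is empty.

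Suppose instead that the range means lying below the time-specific limits. Then nothing overlaps at the moment of starting. But the limit moves from 6 to 8 once 6 h have passed, and the text does not say which limit then governs stopping.

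**The case against.** **Overcorrection is acted on outside Table 2.** This stands. Section 11b requires case-by-case management of any overcorrection whatever the dose clock, and also provides for dextrose when sodium climbs too fast. A reader might infer that an SAE could pass with no action required; the document does not support that. But the only numbers behind the general sentence are counted from a dose, and management can follow only once the rise has been noticed.

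**The 24 h might mean morning to morning.** On that reading paths A to C are not overcorrections, since their 0600 increments never exceed 8. The definition names no start time, so any 24-h window is the plain reading, but it is not stated.

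**The target range is not said to be 5–8.** This also stands. That figure is a rate over 24 h, +7 in 6 h is faster than that rate, and the wording about falling back suggests that sodium has first left the range. The fair criticism is an undefined term. A reader might infer that any started infusion already meets its stop rule; even with 5–8 that fails for 6-h rises above 8 and for the 12-h trigger.

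**Infusion duration does not enter the main safety outcome.** Correct. Table 3 counts correction leading to therapy, so an unclear stop rule does not change that count.

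**The paths are constructed.** They are, and B and C need a large overnight rise although doses are given in the morning. The documents give no basis for a frequency.

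**The full protocol (version 16) or the cited manufacturer advice may settle this.** A definition of the target range may be there. The difference between the two clocks is printed in the article itself.

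**Conclusion.** The point holds in a limited form. With the 24-h definition read as any window, a rise spanning two doses can meet the SAE definition while meeting no Table 2 row and leaving every 0600-to-0600 increment at or below 8. The plain example gives +11, and the most extreme path on the sampling grid used gives +16. These sizes show what the rules allow, not how often it would happen. The gap is the absence of a numeric trigger before the SAE and of a check that reliably detects it; the duty to manage recognised overcorrection is in place.

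The stop rule is a secondary defect of definition. Only if the target range is the 5–8 mmol/L rise do start and stop coincide, and then only for 6-h rises above 6 and up to 8.

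**What to change.** Reconcile Table 1, Table 2 and the text of sections 11a and 11b on three points:

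1. The reference point for the rise, and whether 24 h means any window or morning to morning, so that the SAE definition and the Table 2 triggers can be read together across doses.
2. A running 24-h sodium difference in the daily treatment form, calculated from the samples already planned at 6–8 h intervals after tolvaptan.
3. The meaning of the target range in the stop rule, stated so that it is consistent with the start triggers.

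The investigators and the DSMB choose the values; none is proposed here. The cost is a wording amendment, one derived field in the form and some additional alerts. No extra blood samples are needed.
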